### **11.3 Measurement of Effect/Response**

Prostate/prostate tumor dimensions in cm should be calculated from physical exam and must be recorded on the diagrams found on the data collection forms for initial and follow-up evaluation of the patient. After study entry, disease activity evaluations will be made and recorded using the following criteria:

- 11.3.1** No Evidence of Disease (NED): no clinical evidence of disease on digital rectal examination.
- 11.3.2** Equivocal Disease (ED): this rating will be assigned under the following two circumstances.
- If abnormalities are present on the prostate digital rectal examination but are thought to be abnormal due to treatment and felt not to represent tumor.
  - If clinical evidence of residual tumor is present but this has regressed from a previous examination (*initial registration*)
- 11.3.3** Progressive Disease (PD): this rating will be assigned when there is clinical evidence in the prostate gland of disease progression or recurrence measured by a 25% or greater increase in the product of the two largest perpendicular diameters of the prostate. Only those patients with progressive disease on digital rectal examination will be scored as digital rectal examination failure. The time of failure will be backdated to the first occurrence of equivocal disease after a prior normal examination or to the end of radiation therapy treatment if a normal digital rectal examination was never achieved.
- 11.3.4** Time to Disease-Free Survival: Time to the disease-free survival will be measured from the date of randomization to the date of documentation of progression (local progression, distant failure, and PSA failure) or until the date of death (*from other causes*). (7/14/08)
- 11.3.5** Time to Complete Response (CR): Time in months from randomization to documentation of no evidence of disease (*NED*).
- 11.3.6** Time to PSA Failure: Time in months from randomization to PSA failure as defined below:
- 11.3.6.1** A rise in PSA on at least two consecutive occasions above the nadir. In patients who have been declared a PSA relapse, every effort should be made to withhold further Rx until clinical relapse is evident. When this impossible, the site of failure should be ascertained before instituting further Rx. This may necessitate a bone scan, CT and prostate biopsy.

- 11.3.6.2** The rises in PSA must exceed 1ng/ml above the nadir.
- 11.3.6.3** Failure of the PSA to reach 4 ng/ml or less at 18 months.

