- 11.3.7** Time to Second PSA Failure:  
The time from randomization to second PSA failure as defined below  
(*after institution of relapse therapy*):
- 11.3.7.1** A rise in PSA on at least two consecutive cases above the nadir (*after initiation of relapse therapy*).
- 11.3.7.2** The rises in PSA must exceed 1 ng/ml above the nadir.
- 11.3.7.3** Failure of the PSA to reach 4 ng/L or less at 18 months.
- 11.3.8** Time to Local Progression: The time to progression will be measured from the date of randomization to the date of documented local progression as determined by clinical exam.
- 11.3.9** Time to Distant Failure:  
The time to distant failure will be measured from the date of randomization to the date of documented metastatic disease.
- 11.3.10** Time to Overall Survival: (7/14/08)  
The time to overall survival will be measured from the date of randomization to the date of death due to any cause. All patients will be followed for survival. Every effort should be made

to document the cause of death. Post-mortem examination will be carried out when feasible and a copy of the final autopsy report sent to RTOG.

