## 13.7 Study Endpoints (7/1/97) (7/14/08)

The primary endpoint for this trial is overall survival, on which the sample size is calculated (See Section 11.3.10 for the definition). The absolute survival with failure of death from all

15

causes is a secondary endpoint. We also consider the time to second PSA failure defined in Section 11.3.7 as a secondary endpoint for the trial. The collection of these data allows us to examine the hypothesis that the second PSA failure is a surrogate for death from prostate cancer. With an adequate long period of follow-up, we should be able to study the relationship among these times to endpoints.

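### The second-PSA-failure threshold in 11.3.7.3 is written as 4 ng/L, 1000-fold below the 4 ng/ml of the matching first-failure item; its unit, and the start of its 18 months, need to be stated

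*Protocol*

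**What the plan says.** Section 11.3.6 of the protocol defines first PSA failure and Section 11.3.7 defines second PSA failure, each through three parallel items.

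- **First failure.** The endpoint is the "Time in months from randomization to PSA failure as defined below". Item 11.3.6.3 is "Failure of the PSA to reach 4 ng/ml or less at 18 months".
- **Second failure.** The endpoint is "The time from randomization to second PSA failure as defined below", with the qualifier "after institution of relapse therapy" in the heading text. Item 11.3.7.1 repeats that idea for the nadir ("after initiation of relapse therapy"). Item 11.3.7.2 is "The rises in PSA must exceed 1 ng/ml above the nadir". Item 11.3.7.3 is "Failure of the PSA to reach 4 ng/L or less at 18 months".

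The definition is in use. Section 13.2.2.6 lists freedom from second PSA relapse as a secondary endpoint and points to 11.3.7. Section 13.4.2 tests it with a log-rank test at 0.025 and models it by the Fine and Gray method. Section 13.7 wants the data in order to "examine the hypothesis that the second PSA failure is a surrogate for death from prostate cancer".

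**The concern.** Items 11.3.6.3 and 11.3.7.3 use the same words and the same number but different units. The odd unit sits in the decision threshold of an endpoint that is to be tested, so it matters more than a slip in background text. An analyst or programmer who takes 11.3.7.3 at face value would apply a cut-off three orders of magnitude below the one evidently meant.

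The second, smaller matter is that 11.3.7.3 names a time point without saying what it is counted from. Item 11.3.7.1 carries its own reference to relapse therapy; 11.3.7.3 depends on the heading for it.

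At stake are the event status, and for some men the event date, in the second-PSA-relapse comparison and in the study of its relation to prostate cancer death.

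**Working it through.** **Inputs.** 11.3.6.3: 4 ng/ml at 18 months. 11.3.7.3: 4 ng/L at 18 months. 11.3.7.2: a rise of more than 1 ng/ml.

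**1. Unit conversion.** With 1 L = 1000 ml, 4 ng/L = 4/1000 = 0.004 ng/ml.

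**2. Against the first-failure item.** 4 / 0.004 = 1000.

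**3. Against the neighbouring item.** 1 / 0.004 = 250. The written threshold is 250 times smaller than the rise that 11.3.7.2 requires before an increase counts.

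**4. Who is classified differently.** The two thresholds disagree for any man whose PSA at the check is above 0.004 ng/ml but not above 4 ng/ml. For illustration:

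| PSA at 18 months | 11.3.7.3 as written (0.004 ng/ml) | At 4 ng/ml |
|---|---|---|
| 0.1 ng/ml | item met | item not met |
| 1 ng/ml | item met | item not met |
| 5 ng/ml | item met | item met |

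**5. How the items combine.** Section 11.3.7 does not say whether its items are joined by *and* or *or*.

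- If 11.3.7.3 alone is enough, every man in the range of step 4 becomes a failure.
- If all three items are needed, only men who already meet the rise criteria can be affected. For them the written threshold screens out far fewer than 4 ng/ml would.

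In both cases the error runs one way: everyone above 4 ng/ml is also above 0.004 ng/ml, so the literal text can only add failures.

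**6. Start of the 18 months.** The heading of 11.3.7 limits second failure to the period after relapse therapy has begun. A check made before that therapy therefore cannot yield a second failure. The heading does not say in terms that the 18 months are counted from that start. That is the natural reading, but it is left to inference.

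**7. Dependence of the plan's figures.** The protocol gives no sample size, event count or power for second PSA failure, so there is no stated figure to reproduce. The 716 deaths in 13.4.1 concern overall survival and do not use this definition.

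**The case against.** The strongest reply is that no one reading 11.3.6 and 11.3.7 together would apply 0.004 ng/ml. The two sections mirror each other item by item, 11.3.7.2 is in ng/ml, and the intended value is plain. Section 1.3 also gives a PSA cut-off of 4 per litre with a unit prefix that appears to be lost. Since 4 µg/L equals 4 ng/ml, a per-litre unit with a damaged prefix is a possible origin here too, though the text cannot prove it. This stands as an explanation, and it is why the point is called a probable slip. It does not remove the need to correct an operative threshold that nothing else in the protocol corrects.

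Three stronger readings are tempting, and the protocol does not support them.

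- **That the randomization clock is wrong.** A reader might infer that, with time counted from randomization, the 18-month check falls before relapse therapy for men who relapse late. The heading of 11.3.7 rules this out. Counting event time from randomization is also the protocol's practice for its other time-to-event endpoints and is not a fault. An estimate of how many men relapse before month 18 adds nothing, because it matters only under the excluded reading.
- **That nearly every man on relapse therapy fails.** This needs both literal use of the slip and 11.3.7.3 being sufficient alone. The text does not settle the second condition.
- **That the analyses become meaningless.** Nothing shows that the written unit was ever applied. The endpoint is one of nine listed secondary endpoints, and 13.7 presents surrogacy as a hypothesis to be examined.

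**Conclusion.** The point holds as an error of unit in an endpoint definition, with a lesser gap in the stated time origin. The unit discrepancy is exactly 1000-fold and needs no assumption beyond the conversion. Its effect on classification is conditional: it assumes that the text is applied literally, and it is largest if 11.3.7.3 suffices by itself. Under those conditions men with well-suppressed PSA on relapse therapy would be counted as second failures. This would inflate the events in 13.2.2.6 and blur the relation to prostate cancer death that 13.7 sets out to study. The primary endpoint and the 716 deaths do not change. The correction should be made because the threshold is operative and the change is cheap, not because harm to the results has been demonstrated.

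**What to change.** Reword 11.3.7.3 along these lines: PSA not at or below 4 ng/ml when checked 18 months after relapse therapy was started. Leave the event time in 11.3.7 counted from randomization. This aligns the unit with 11.3.6.3 and 11.3.7.2 and writes out what the heading already implies. It would be sensible in the same edit to say how the three items combine.

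The cost is one line of text. Footnote g of 11.1 already requires all PSA values, at least every six months, and a statement of whether hormonal therapy was begun for relapse. The one thing to confirm is that the start date of that therapy can be recovered from the follow-up forms. No sample size, event count or power changes.

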### 11.3.11 Time to Disease Specific Survival: (7/1/97) (7/14/08)

The time to disease specific survival will be measured from the date of randomization to the date of the following events.

- a. The following will be considered as endpoints in assessing disease specific survival (DSS), i.e., events:
  - Death certified as due to prostatic cancer.
  - Death due to complications of treatment, irrespective of the status of malignancy.
  - Death from unknown causes with active malignancy (*clinical or biochemical progression*).
  - Death from unknown causes with previously documented relapse (*either clinical or biochemical*).
- b. The following will be considered as events that may be related to death from prostate cancer. They will be added into the previous definition for a separate analysis.
  - Death from unknown causes without reported relapse.
  - Death from other causes with previous documented relapse (*either clinical or biochemical*) but inactive at the time of death.

## 12.0 DATA COLLECTION (4/1/95, 7/1/97)

| Item                                         | Due                      |
|-----------------------------------------------------|---------------------------------|
| Demographic Form (A5)                               | Within 1 week of study entry    |
| On Study Form (I1)                                  | Within 2 weeks of randomization |
| Pathology Report (P1)                               |                                 |
| Pathology Slides/Blocks (P2)                        |                                 |
| Surgical Operative Report (S2)*                     |                                 |
| Surgical Pathology Report (S5)*                     |                                 |
| * If node dissection or sampling was performed      |                                 |
| + Pretreatment Sexual Adjustment Questionnaire (SA) |                                 |

Preliminary Dosimetry Information: Within 1 week of  
 start of RT RT Prescription (*Protocol Treatment Form*) (T2)  
 Films (*simulation and portal*) (T3)  
 Calculations (T4)  
 Interim Report (F9) (*Arm 1*)

## Hormone Flowsheet (**M1**) (*Arm 1*)

Radiotherapy Form (**T1**)

Within 1 week of RT end

Final Dosimetry Information:

Daily Treatment Record (**T5**)

Isodose Distribution (**T6**)

Boost Films (*simulation and portal*) (**T8**)

|                                                                                    |                                                                                                                                          |
|------------------------------------------------------------------------------------|------------------------------------------------------------------------------------------------------------------------------------------|
| Hormone Flowsheet ( M1 )                                                    | Upon completion of hormone therapy, thereafter with each follow-up form for 6 mos. following completion of hormones.                     |
| Follow-up Form ( F1 )
, every 6 mos during years 3-5 then death.         | Upon completion of radiotherapy, then every 3 mos during year 1, every 4 mos. during year 2 annually. Also at progression/relapse and at |
| + Post Rx Sexual Adjustment Questionnaire ( SB )                            | Pre RT ( Arm 1 ); upon completion of treatment, then q 3 months during year 1, q 4 months in year 2.                              |
| Pathology Report/Rebiopsy ( P1 )
Pathology Blocks/Rebiopsy ( P2 ) | At 2 years post RT                                                                                                                       |
| Autopsy Report ( D3 )                                                       | As applicable.                                                                                                                           |
| + Completed by the patient. ( QOL assessments discontinued 7/1/97 ).        |                                                                                                                                          |

## **13.0 Statistical Considerations**

### **13.1 Study Design**

The objectives of the trial are described in Section 2.0. They can be met by a randomized comparison of two groups testing neoadjuvant total androgen suppression (*TAS*) before/during RT versus RT alone.

Treatment allocation will be done by randomized permuted blocks within strata to balance for prognostic factors. Stratification will be done by PSA (< 4, 4-20) and differentiation (*well*, *moderate*, *poor*), and nodal status (*N0*, *NX*).

## **13.2 Study Endpoints (7/14/08)**

### **13.2.1 Primary Endpoint**

Overall Survival (See section 11.3.10)

### **13.2.2 Secondary Endpoints**

**13.2.2.1** Disease-specific survival (See section 11.3.11)

**13.2.2.2** Local progression (See section 11.3.8)

**13.2.2.3** Distant failure (See section 11.3.9)

**13.2.2.4** Freedom from PSA failure (See section 11.3.6)

**13.2.2.5** Freedom from second clinical relapse (local progression and/or distant failure)

**13.2.2.6** Freedom from second PSA relapse (See section 11.3.7)

**13.2.2.7** Disease-free survival (See section 11.3.4)

**13.2.2.8** Prostate re-biopsy at two years

**13.2.2.9** Effect on sexual function (See section 11.3.12)

## **13.3 Sample size and accrual (7/14/08)**

**As of July 1, 1997, the sample size is 1980 (See section 13.7).**

*TAS* is known to lower PSA but time to initial PSA failure may not be a good indicator of ultimate clinical outcome. If neoadjuvant *TAS* is successful, there should ultimately be a positive impact on cause-specific survival. Because of the expected mortality due to other causes in this population, an improvement in cause-specific survival may be difficult to detect if overall survival were used as the primary endpoint. Clearly identifying deaths due to prostate cancer is difficult because metastasis is usually to the bone rather than to a vital organ.

The primary endpoint for this trial upon which sample size is based is defined to be closely associated to death due to prostate cancer. Review of causes of death by the study chair will be necessary.

The following will be considered treatment failures:

1. Death certified as due to carcinoma of the prostate.
2. Cancer associated death.
3. Death due to complications of treatment irrespective of the status of the cancer.
4. Progressive metastatic disease while on any antitumor therapy.
5. Rising PSA while on any antitumor therapy.

Average failure rates were obtained from other datasets with the recognition that they may not be identical with what might be expected from this population.

Death rate: The death rate from early stage prostate patients from RTOG 77-06 had an average annual death rate of 0.045. Fourteen of the 46 reported deaths were categorized as due to prostate cancer. The prostate cancer death rate and other cause death rate were found by multiplying 0.045 by 14/46 and (46-14)/46.

Rate of first failure: This was taken to be 0.12 (*communication [name]*).

Rate of second failure while on hormonal therapy: This was taken to be 0.24 (*communication [name]*).

The goal of the trial is to be able to detect a lowering of the failure rates by 33% with 90% power using a two-sided test. Using methods described by Lakatos, **a total of N=670 patients are required** to be accrued uniformly over three years and followed for three additional years before final analysis of treatment failure. This includes an estimate of 10% unevaluable patients. The expected numbers of events on the two arms at the time of final analysis are 71 and 39.

The Sexual Adjustment Questionnaire (SAQ) has five subscales; desire, activity level, arousal, orgasm, and satisfaction, that will be used to assess the effect of treatment, changes in serum testosterone, and other patient characteristics on patient's perception of quality of sexual function. The SAQ will be applied pretreatment, post radiotherapy, every three months for the first year of follow-up, and every four months for the second year of follow-up. Because it is unknown when a critical or defining change in sexual function occurs or remains stable all eight follow-up questionnaires are required and necessary for comparison of groups. Submission of the initial SAQ on RTOG 91-16 was 90% and 67% on RTOG 90-20. The submission of the follow-up questionnaires ranges from 40-90%.

This study should have sufficient numbers of patients completing the two-year follow-up SAQ to find a difference of at least one in the mean responses between groups for any of the five subscales. The estimated variance and completion rates will impact the required sample size. Because there is no reliable estimate of the SAQ response variance and completion rates will vary these parameters will be estimated after 200 patients have been randomized to this trial. These estimates will be utilized to determine whether additional patients will be accrued to the SAQ component. The results of this analysis will be presented to the Data Monitoring Committee (DMC).

Functional status, the ability to have an erection, will be measured with a 'yes/no' response at baseline and at each follow-up. It is assumed that at least 50% of all patients will enter the study with the ability to have an erection and 70% of these patients on the RT alone arm will retain this function. If 300 patients that enter the trial with the ability to have an erection are analyzable at 2 years, then this trial will have at least 80% statistical power to detect at least a 15% (*absolute*) reduction in the retention of function in the RT+TAS arm, testing at the 0.05 (*one-sided*) level.

## 13.4 Analysis Plan (11/13/00) (11/17/05) (7/14/08)

Analyses of time to treatment failure will use the log-rank test and the Cox proportional hazards model. All hypothesis testing will be two-sided. Exploration of the effects of pretreatment prognostic factors such as stage, Gleason score and PSA will be done using the Cox proportional hazards model. There will also be exploratory analyses of the different reasons for treatment failure.

Interim accrual and morbidity reports will be done at least semi-annually prior to the RTOG group meeting. The report will describe accrual by institution and project completion of accrual. It will give the distribution of pretreatment characteristics and a tabulation of toxicities.

Three interim treatment comparisons shall be performed when we observe 29%, 60% and 80% of the 261 required maximum number of prostate cancer related deaths. The first interim analysis is projected to take place at the second year after the closure (*every patient has at least one year of follow-up*). The second and third interim analyses are projected to take place at the fifth year (*4 years of follow-up*) and seventh year (*6 years of follow-up*) after the closure, respectively. For each of these interim analyses, toxicity, treatment delivery and efficacy statistics will be reported to RTOG DMC. The boundary for early stopping (*or the nominal significance level for the test*) will be computed based on the observed number of deaths according to the O'Brien-Fleming alpha spending function approach. If the difference is highly significant, i.e., p value less than the

nominal level, the responsible statistician will recommend to DMC that the study be written up for publication.

Analysis of SAQ will be performed on all patients that complete baseline questionnaires. The analysis will utilize analysis of variance, and repeated measures analysis of variance to examine differences in treatments. SAQ will be examined for responsiveness in follow-up and correlation to changes in serum testosterone. Analysis of SAQ by subgroups will be undertaken for groups with sufficient sample size.

The study was designed for three interim analyses of the primary endpoint, disease-specific survival (death due to prostate cancer) when we observe 29% (76), 60% (157) and 80% (209) of the 260 required maximum number of prostate cancer related deaths. D'Amico et al showed a statistically significant improvement in disease-specific survival with six months of total androgen blockade given two months before, during and after radiation therapy in a similar patient population. Based on this result, the disease site and study chairs requested an early look at disease-specific survival. This request was presented at the RTOG Data Monitoring Committee (DMC) in June 2005. The RTOG DMC approved an early analysis of the primary endpoint. Thus the first interim analysis is now planned to be done with 66 deaths. The boundary for early stopping (or the nominal significance level for the test) will be a modified Haybittle-Peto boundary. The stopping boundary of each of the three interim analyses is 3.291 (for a nominal significance level of 0.001) and the boundary for the final analysis is 1.96 which makes the overall significance level 0.051.

**All eligible patients who are randomized to the study will be included in the comparison of treatment arms (intent-to-treat analysis).**

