### **3.0 PATIENT SELECTION (9/8/98, 11/13/00)**

#### **3.1 Conditions for Patient Eligibility**

- 3.1.1** Eligible patients will be those with histologically confirmed locally confined adenocarcinoma of the prostate. Included will be patients with primary tumors confined to the prostate, clinical stage T1b,1c, 2a or 2b.
- 3.1.2** Nodes evaluated negative by imaging methods will be classified as Nx. Nodes evaluated negative by surgical sampling will be classified as N0.
- 3.1.3** Karnofsky performance status  $\geq 70$ .
- 3.1.4** PSA is mandatory for patient eligibility; (*PSA must be  $\leq 20$* )
- 3.1.5** No prior hormonal therapy, radiation or chemotherapy.
- 3.1.5.1** Prior finasteride for prostate hypertrophy is allowed if discontinued at least 60 days prior to randomization.
- 3.1.5.2** Prior testosterone administration is allowed if at least 90 days have elapsed since last administration (*testosterone effect will have receded by 90 days*).
- 3.1.6** No evidence of distant metastasis or other synchronous primary. Patients with prior invasive malignancy who have been disease free for at least 5 years may be eligible. Before entry, these patients must be approved by the study chairman.
- 3.1.7** Treatment must begin within 21 days after randomization.
- 3.1.8** Patients must sign a study-specific informed consent form.
- 3.1.9** ALT must be within 2x upper normal limits.

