#### **3.2 Conditions for Patient Ineligibility (10/13/95)**

- 3.2.1** Stage T1a or  $\geq$  T2c disease.
- 3.2.2** Lymph node involvement (*N1 - N3*).
- 3.2.3** Evidence of distant metastasis. (*M1*)
- 3.2.4** PSA  $> 20$ .
- 3.2.5** Radical surgery or cryosurgery for carcinoma of the prostate, previous irradiation, antiandrogen therapy or chemotherapy.
- 3.2.6** Previous or concurrent cancers other than basal cell or squamous cell skin carcinoma. Patients with squamous cell carcinomas must be NED for a minimum of two years prior to study entry.
- 3.2.7** Major medical or psychiatric illness which, in the investigator's opinion, would prevent completion of treatment and would interfere with follow-up.
- 3.2.8** Karnofsky performance status of  $< 70$ .

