### 13.8.2 Sample Size

For the primary endpoint, disease specific survival, we will use a two-sided log-rank test to detect the treatment effect of 33% reduction in hazard of death from prostate cancer with a significance level of 0.05 and a power of 90%. Using Lakatos' method (*assuming there is no drop-in and noncompliance, and loss of follow-up rate equals to the other cause mortality rate*), a total of 1779 patients is required to be accrued uniformly over five years and followed for additional eight years before the final analysis. Accounting for possible 10% unevaluable cases, **the total required sample size is 1980 for both arms of the study.**

With the proposed sample size, we will be able to detect a 16.7% average reduction in hazard of death from all causes with 75% power. (*However, if the reduction in death from all causes is 11%, a formidably large sample size will be required*).

If the current percentage (36%) of patients with Gleason 7-10 holds for the study, we will expect to enter 640 such evaluable patients. With this expected number of patients, we will be able to detect a 40% reduction in hazard of death from prostate cancer for patients with Gleason 7-10 with a statistical power of 80%. On the other hand, we will be able to detect a 20% reduction in hazard of absolute survival with statistical power of 53% for patients with Gleason 7-10.

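### The primary survival comparison is called intent-to-treat but keeps only eligible patients, and one eligibility condition is met or failed after randomization

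*Protocol*

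**What the plan says.** Protocol section 13.4 closes its general text with the rule for the arm comparison: "All eligible patients who are randomized to the study will be included in the comparison of treatment arms (intent-to-treat analysis". Section 13.4.1, which sets out the overall survival test, names no other population. Section 13.4.3 also uses eligible patients as its denominator, for the re-biopsy rate.

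The primary endpoint is all-cause death. Section 11.3.10 states "The time to overall survival will be measured from the date of randomization to the date of death due to any cause", and adds "All patients will be followed for survival".

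The eligibility list in section 3.1 includes 3.1.7, the start of treatment no later than 21 days after randomization. The schema page applies this to both arms, and section 5.1 repeats it. Under section 6.1, radiotherapy in Arm 1 begins two months after the drugs, so in that arm the condition can only refer to the drugs. Under section 6.2 it refers to radiotherapy in Arm 2.

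Section 13.8.2 plans the numbers: "a total of 1779 patients is required to be accrued uniformly over five years and followed for additional eight years" and then, "Accounting for possible 10% unevaluable cases", "the total required sample size is 1980 for both arms of the study".

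On prior cancers, 3.1.6 says "Patients with prior invasive malignancy who have been disease free for at least 5 years may be eligible", subject to the study chairman's approval before entry, and checklist item 12 agrees. Section 3.2.6 lists as a ground for ineligibility "Previous or concurrent cancers other than basal cell or squamous cell skin carcinoma", with no five-year exception.

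**The concern.** Intent-to-treat means everyone randomized, in the arm assigned. An eligible-only set is a different population. It is harmless when eligibility rests on baseline facts judged without regard to arm. Here one condition depends on what happens after assignment, and the event that satisfies it differs by arm: starting drug in one, starting radiotherapy in the other. Section 13.1 compares androgen suppression plus radiotherapy with radiotherapy alone and describes no placebo, so patient and physician know the assignment when treatment is due to start.

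Men who do not start on time may differ in prognosis from those who do. If they leave the analysis in different proportions by arm, the randomized comparison of overall survival is no longer protected. Nothing about the endpoint requires their removal, because death from any cause can be observed in an ineligible man as well as in an eligible one.

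**Working it through.** **1. The plan's own figures.**
- Enrolment: 1779 / (1 − 0.10) = 1977, against 1980 stated. Reproduced to rounding.
- Deaths (13.4.1): HR = ln 0.67 / ln 0.60 = 0.784. Freedman's formula with one-sided α = 0.025 and 90% power gives (1.960 + 1.282)² × [(1 + 0.784)/(1 − 0.784)]² ≈ 717, against 716 stated. Reproduced.

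**2. Can a randomized man leave the analysis after assignment?**
- 3.1.7 is listed as a condition of eligibility, and compliance is known only after randomization.
- 13.4 admits only eligible patients to the comparison.
- Read together, a man who fails 3.1.7 can be excluded.
- 13.8.1 (assumption 2) shows that ineligible patients are found among those already entered and are removed from a count.
- The protocol does not say that eligibility is judged from baseline facts only or without knowledge of arm and outcome. It specifies no comparison of all randomized patients.

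**3. What could this do to the test? Assumed inputs, not from the documents.** Let d1 and d2 be the shares excluded from Arms 1 and 2, and g the hazard of excluded men relative to the average. With no true effect, to first order:

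- remaining relative hazard in arm i: r_i = (1 − d_i·g)/(1 − d_i)
- apparent HR = r_1/r_2
- shift in z = −ln(HR) × √716 / 2 = −ln(HR) × 13.38
- one-sided error = Φ(shift − 1.96)

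| Excluded, Arm 1 vs Arm 2 | g | Apparent HR | Shift in z | One-sided error |
|---|---|---|---|---|
| 5% vs 5% | 1.5 to 3 | 1.000 | 0 | 2.5% |
| 6% vs 4% | 1 | 1.000 | 0 | 2.5% |
| 6% vs 4% | 1.5 | 0.989 | 0.15 | 3.5% |
| 6% vs 4% | 2 | 0.977 | 0.31 | 5.0% |
| 6% vs 4% | 3 | 0.952 | 0.66 | 9.7% |
| 4% vs 6% | 1.5 | 1.011 | −0.15 | 1.7% |
| 4% vs 6% | 3 | 1.051 | −0.66 | 0.4% |

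Worked line, g = 1.5: r_1 = (1 − 0.09)/0.94 = 0.9681; r_2 = (1 − 0.06)/0.96 = 0.9792; HR = 0.9887; shift = 0.0114 × 13.38 = 0.152; Φ(−1.808) = 3.5%.

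The model gives the excluded men the same prognosis in both arms. In it, bias needs exclusion that both differs by arm and is related to prognosis.

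**4. Effect of the fix on timing.** With hazards 0.0639 and 0.0501, five years of uniform accrual and no loss to follow-up (assumed), expected deaths F years after closure are the sum over arms of (N/2) × [1 − (e^(−λF) − e^(−λ(5+F)))/(5λ)]. Setting this to 716 gives F of about 5.5 years for N = 1980 and about 6.6 years for N = 1779. The second figure applies only if the whole 10% allowance were excluded.

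**The case against.** The strongest reply is that eligibility is settled before assignment. Section 5.1 permits registration only once the pretreatment evaluation is complete and the criteria are met. The checklist comes before the treatment assignment and asks about the 21-day start prospectively. Most criteria (T stage, PSA, performance status, ALT, prior therapy) are baseline facts, and exclusion on those, applied alike in both arms, does not break randomization. This stands, and it may keep the number of exclusions small. It does not remove the problem: 3.1.7 as worded can be verified only after randomization, and nothing in 13.4 says that a man who passed the checklist stays in the analysis.

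Three stronger readings are tempting and not supported.

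- A reader might infer that about 200 of 1980 men will be dropped. The 10% is an allowance for unevaluable cases, which the protocol does not define. It dates from the 1997 disease-specific survival design and is not an ineligibility rate.
- A reader might infer that the false-positive rate is inflated. Every exclusion share and relative hazard above is assumed, and reversing the arms makes the test conservative.
- A reader might infer that the conflict between 3.1.6 and 3.2.6 biases the comparison. It applies equally to both arms, and chair approval and the checklist largely settle it before entry. It is a drafting matter about who counts as eligible.

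A statistical analysis plan might add an all-randomized analysis. It would not make the protocol's label correct.

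**Conclusion.** The point holds as a rule that is wrong as written. The population for the primary test is mislabelled, and the text allows men to be removed for post-assignment behaviour that is defined differently in each arm. That much follows from sections 3.1.7, 6.1, 6.2 and 13.4 alone. The absence of blinding is inferred from the arms, since the protocol does not use the term.

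The consequence is a possibility, not a demonstrated bias. Depending on assumptions that the documents cannot settle, the one-sided error could be unchanged, above 2.5% or below it. The 3.5% to 9.7% range belongs to one assumed pattern (6% versus 4%, more exclusions from Arm 1). The change is worth making because it removes the question at little cost.

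**What to change.** - **Primary analysis.** In 13.4 and 13.4.1, make all randomized patients, analysed in the arm assigned, the population for overall survival, and count the 716 deaths in that set.
- **Sensitivity analysis.** Keep the eligible-only comparison under that name and drop the intent-to-treat label from it.
- **Secondary time-to-event endpoints.** Use the all-randomized set only where follow-up of ineligible men is actually collected. Section 11.3.10 promises survival follow-up for everyone; the protocol makes no such statement for PSA or progression.
- **Separately**, reconcile 3.1.6 and checklist item 12 with 3.2.6, so that the eligible set used for sensitivity is well defined.

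**Cost.** Revised wording and one additional analysis. The death target, significance level and power calculation are unchanged, and deaths would accrue no later than under the restricted set. The drawback is slight dilution of the effect if some ineligible men cannot benefit from the treatment.
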